## Abstract

**Background:**

Recent international guidelines recommend intra-articular corticosteroid injections for patients with hip osteoarthritis who have moderate to severe pain and do not respond satisfactorily to oral analgesic/anti-inflammatory agents. Of the five available randomized controlled trials, four showed positive effects with respect to pain reduction. However, intra-articular injection in the hip is complex because the joint is adjacent to important neurovascular structures and cannot be palpated. Therefore fluoroscopic or ultrasound guidance is needed.

The systemic effect of corticosteroids has been studied in patients with impingement shoulder pain. Gluteal corticosteroid injection was almost as effective as ultrasound-guided subacromial corticosteroid injection. Such a clinically relevant effect of a systemic corticosteroid injection offers a less complex alternative for treatment of patients with hip osteoarthritis not responsive to oral pain medication.

**Methods/Design:**

This is a double-blinded, randomized controlled trial. A total of 135 patients (aged > 40 years) with hip osteoarthritis and persistent pain despite oral analgesics visiting a general practitioner or orthopaedic surgeon will be included. They will be randomized to a gluteal intramuscular corticosteroid injection or a gluteal intramuscular placebo (saline) injection. The randomization will be stratified for setting (general practitioner and outpatient clinics of department of orthopaedics). Treatment effect will be evaluated by questionnaires at 2, 4, 6, and 12 weeks follow-up and a physical examination at 12 weeks. Primary outcome is severity of hip pain reported by the patients at 2-week follow-up. Statistical analyses will be based on the intention-to-treat principle.

**Discussion:**

This study will evaluate the effectiveness of an intramuscular corticosteroid injection on pain in patients with hip osteoarthritis. Patient recruitment has started.

**Trial Registration:**

This trial is registered in the Dutch Trial Registry: number NTR2966.

## Background

Recent international guidelines recommend intra-articular (IA) corticosteroid injections for patients with hip osteoarthritis (OA) who have moderate to severe pain and no satisfactory response to oral analgesic/anti-inflammatory agents [1]. Of the five randomized controlled trials (RCTs) on this subject [2-6], four showed clinically significant positive effects with respect to pain reduction (effect size up to 1.5 at 1 week follow-up) [2,4-6] and one showed no clinical benefit of an IA injection [3]. In the RCT that showed no clinical benefit of an IA injection, patients were biased towards a negative result having been informed they would receive priority for surgery if their pain worsened after injection [3].

Because the hip joint is adjacent to important neurovascular structures and cannot be palpated, IA injection under fluoroscopic or ultrasound guidance is advised. However, these techniques are not always available, especially in a primary care setting. Moreover, apart from being complex, an IA hip injection can be painful for the patient and can lead to septic arthritis. An effective but simpler administration technique would be a welcome addition to the current methods to treat episodes of increased pain in hip OA.

A double-blind RCT in patients with subacromial impingement shoulder pain showed almost equal effectiveness of ultrasound-guided subacromial corticosteroid injection compared to gluteal (systemic) injection [7]; this effect was also reported in an earlier study [8]. In addition, an equal or even more pronounced pain decrease was found in patients with concurrent hip OA or chronic low back pain in an RCT assessing the effectiveness of a local corticosteroid injection in patients with greater trochanteric pain syndrome [9,10]. These results indicate a systemic effect of corticosteroids on pain in OA.

A clinically relevant effect of a systemic corticosteroid injection, offers a less complex alternative for treatment of patients with hip OA who are not responsive to oral pain medication. Since IA hip injection is not standard care in the Netherlands, we decided to conduct a trial comparing intramuscular (IM) corticosteroid injection versus IM placebo injection.

### Primary objective

This RCT will assess the effectiveness of an IM gluteal corticosteroid injection versus an IM gluteal placebo injection for pain in patients with hip OA who have moderate to severe pain and no satisfactory response to oral analgesic/anti-inflammatory agents during 12-weeks follow-up.

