### Outcomes

#### Questionnaires at baseline, 2, 4, 6 and 12 weeks

All outcomes are measured at baseline and at 2, 4, 6 and 12 weeks follow-up. The primary outcome is severity of hip pain reported by the patient at 2 weeks. This will be measured with two validated questionnaires: an 11-point numerical rating scale (NRS) in rest and on walking (0-10, where 0 equals no pain) [12], and the Western Ontario and McMaster University Osteoarthritis Index (WOMAC) pain subscale [13]. The WOMAC pain subscale will be converted to a 0-100 score, where 0 equals no symptoms. The WOMAC is recommended by the Osteoarthritis Research Society for use in clinical trials in patients with hip OA to measure pain and disability [13].

Secondary outcomes include the primary outcomes at 4, 6, and 12 weeks follow-up. Additional secondary outcomes are the disease-specific WOMAC function and stiffness subscales [13]. Both the function and stiffness subscale of the WOMAC will be converted to a 0-100 score. Data on pain and function will also be obtained with the Hip disability and Osteoarthritis Outcome Score (HOOS) [14], which was developed as an extended version of the WOMAC to evaluate the whole domain of patient-relevant outcome in young and active patients and is validated in the Dutch language [15].

For patients' perceived recovery a 7-point Likert scale will be used (score range 1 = 'worse than ever' to 7 = 'major improvement') [9,16]. Quality of life will be measured with the Euroqol (EQ-5D) [17]. Constant and intermittent pain will be obtained with the questionnaire Intermittent and Constant Osteoarthritis Pain (ICOAP) taking into account both pain intensity and impact on quality of life [18]. Patients' medical consumption will be registered and adverse reactions noted [9,16]. For this, a questionnaire will be used that covers the known local and systemic adverse reactions to corticosteroids. Data on daily pain and pain medication use will be obtained with a diary during the first 2-weeks follow-up.

Another secondary outcome is the difference in percentage of responders as defined by the OMERACT-OARSI (improvement in at least 2 of the 3 following domains: ≥20% improvement in WOMAC pain, ≥20% improvement in WOMAC function, or markedly improved on the patients' global assessment) [17].

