### Sample size

Data from the Qvistgaard et al. study (patients with hip OA from primary care and secondary care) were used to calculate our sample size [6]. That study showed a baseline standard deviation (SD) of 20 for pain at rest and at walking (0-100 visual analogue scale; VAS). Assuming a minimal clinically relevant difference of 10 points (effect size 0.5), 64 patients per group will be needed to show a statistically significantly difference using 80% power and with a 5% alpha.

In that same study [6] the WOMAC total score (0-96) was used with an SD of 15. Standardized to a 0-100 score this SD is almost 16. Assuming an SD of 16 and an 8-point difference as clinically relevant (effect size 0.5), the same sample size is needed.

We checked these scores in a Dutch study population with hip OA, i.e. those with a K-L score of the hip ≥ 2 and a VAS pain score ≥ 30, participating in the GOAL study [22]. This showed they had a mean VAS score of 56.4 with an SD of 19.3, a mean WOMAC pain score of 51.2 with a SD of 16.4; these data are very similar to the SDs in the study of Qvistgaard et al. Therefore, in the planned trial, we will include 135 patients, anticipating only 5% loss to follow-up based on the relatively short follow-up and earlier experience with loss to follow-up [22,23].

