### Data analyses

Data analysis will be performed based on the 'intention to treat' principle.

Descriptive statistics will be used to describe patient's characteristics, items of physical examination, and the severity of radiologic hip OA.

Linear mixed models will be used for repeated measures to analyze the continuous outcome measures. Fixed effects will be time, time by therapy and the covariates we adjust for. For patients lost to follow-up, we will include all observed data in the analysis. Adjustment will be made for those baseline variables that change the effect estimate by more than 10%. Similar analyses with Generalized Estimating Equations techniques for repeated measures will be done for dichotomous outcome measures.

Subgroup analyses for setting will be analyzed by assessing interaction effects between type of intervention and setting on the primary outcomes; in addition, the estimates will be shown for both settings separately. We realize that these subgroup analyses will remain solely explorative because our sample size is not directed to powerful subgroup analyses.

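### The primary objective covers 12 weeks and the primary outcome is week 2; the analysis section ties its mixed model to neither and leaves the primary contrast unnamed

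*Protocol article*

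**What the plan says.** Four places in the protocol article bear on the primary question.

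- **Primary objective.** The trial will compare the two injections for pain in patients "who have moderate to severe pain and no satisfactory response to oral analgesic/anti-inflammatory agents during 12-weeks follow-up". No time point within the 12 weeks is singled out.
- **Abstract and Outcomes.** Both fix week 2: "Primary outcome is severity of hip pain reported by the patients at 2-week follow-up" and "The primary outcome is severity of hip pain reported by the patient at 2 weeks". Outcomes then adds: "Secondary outcomes include the primary outcomes at 4, 6, and 12 weeks follow-up".
- **Data analyses.** "Linear mixed models will be used for repeated measures to analyze the continuous outcome measures", and "Fixed effects will be time, time by therapy and the covariates we adjust for". The section does not say whether time is a visit factor or a number of weeks, lists no therapy main effect, and does not say which estimate is the primary result. Covariates are those that shift the effect estimate by more than 10%, so baseline pain is not guaranteed a place.
- **Sample size.** A single difference of 0.5 SD is powered, with no time point given.

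**The concern.** The objective points to the whole 12-week course and the outcome definition to one visit. The analysis section, which should settle the matter, describes a model from which several tests can be drawn: the therapy difference at week 2, an average over follow-up, a joint test of all time-by-therapy terms, or a slope. They answer different questions and have different power. An analysis plan written from this article could cite the objective for a 12-week average or the outcome definition for week 2. If the choice were made with unblinded data in hand, the nominal 5% error rate would no longer be secure.

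The covariate rule adds a smaller problem. Baseline pain should be well balanced by randomization, so it may move the estimate by less than 10% and be left out, although it is likely to improve precision.

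**Working it through.** **Inputs from the article (Sample size).** "That study showed a baseline standard deviation (SD) of 20 for pain at rest and at walking" on a 0–100 scale; difference 10 points; 80% power; 5% alpha (taken as two-sided); 64 per group; 5% loss; 135 in total. Visits: "All outcomes are measured at baseline and at 2, 4, 6 and 12 weeks follow-up".

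**Assumed, not in the article.** Equal correlation ρ between any two visits, 0.5 to 0.7 unless stated; complete data; the same SD at all visits; a benefit of 10, 7.5, 5 and 0 points at weeks 2, 4, 6 and 12, or else a constant 10 points.

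**Step 1: the stated sample size.** n = 2(1.96 + 0.8416)² × 20²/10² = 62.8, so 63 per group by the normal approximation. The noncentral t gives 64 (power 0.801; 63 gives 0.795). 128/0.95 = 134.7, so 135. The figure reproduces. Powers below are Φ(effect/SE − 1.96).

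**Step 2: week-2 contrast, time as a visit factor.** The estimate is the true 10 points, whatever happens later.
- Without baseline: SE = 20√(2/64) = 3.54; power Φ(2.83 − 1.96) = 0.81.
- With baseline pain (covariate, or response with arms constrained equal): SE = 3.54√(1 − ρ²). At ρ = 0.3, 0.5, 0.6, 0.7 this is 3.37, 3.06, 2.83, 2.52; power 0.84, 0.90, 0.94, 0.98.

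**Step 3: average of the four follow-up visits, fading benefit.** Mean effect (10 + 7.5 + 5 + 0)/4 = 5.625.
- Without baseline: SE = 20√[(2/64)(1 + 3ρ)/4].
- With baseline: SE = 20√[(2/64)((1 + 3ρ)/4 − ρ²)].

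| ρ | SE, no baseline | Power | SE, with baseline | Power |
|---|---|---|---|---|
| 0.5 | 2.80 | 0.52 | 2.17 | 0.74 |
| 0.6 | 2.96 | 0.48 | 2.06 | 0.78 |
| 0.7 | 3.11 | 0.44 | 1.89 | 0.85 |

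**Step 4: the same average, constant 10-point benefit.** Power without baseline is 0.95, 0.92 and 0.89 at ρ = 0.5, 0.6 and 0.7; with baseline it exceeds 0.99. The average now beats the week-2 test, so the ranking of the two tests depends on the unknown time course.

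**Step 5: time as a number.** With no therapy main effect, the arm difference at week t is δt. Week 2 is then forced to 2/12 = one sixth of week 12. Fitting this model by generalized least squares to the fading profile gives an expected week-2 benefit of −0.19, −0.31 and −0.41 points at ρ = 0.5, 0.6 and 0.7 with baseline included, or −0.66, −0.93 and −1.20 from follow-up visits only, against a true +10. With a constant 10-point benefit and baseline included it gives about 1.3 to 1.5 points. This coding would be unsuitable, but the article does not state it.

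**The case against.** The strongest reply is that the primary time point is already fixed. Week 2 is named twice, the later visits are expressly secondary, and the objective's 12 weeks may simply describe the follow-up period. The outcome definition would normally govern the test. Visit-specific outcomes also suggest time as a factor. On that coding, time plus time by therapy without a therapy main effect is a recognised specification that yields a difference at each visit, and the missing main effect does no harm. Finally, coding and contrasts are often left to an analysis plan, and only a condensed article is available.

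Most of this stands. A reader might infer from the term list that the primary analysis will miss or even reverse the week-2 effect. The article does not support that: it happens only if time is linear and the slope supplies the result, and neither is stated. A reader might also infer that the sample size was calculated for week 2. That is plausible, since one single-visit difference is powered, but Sample size names no visit. The 44–52% power for the average is likewise the unfavourable presentation, without baseline and with a fading effect.

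The reply does not remove the difference in wording between objective and outcome, which is in the printed text. Nor does it cover the covariate rule, which the article states outright and which leaves baseline pain to the data.

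**Conclusion.** The point holds as a matter of alignment. The objective and the primary outcome refer to different periods, and the analysis section does not say which estimate answers the primary question. The natural reading, a visit factor with the week-2 difference, is sound and unbiased. This is therefore a clarification to make before unblinding, of moderate to minor weight, and not a defect that invalidates the analysis.

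Its size depends on the time course. With the assumed fading benefit, moving from week 2 to a follow-up average cuts power from 81% to 44–52% without baseline pain, or from 90–98% to 74–85% with it. With a lasting benefit the average gains power. Always including baseline pain raises week-2 power from about 81% to 84–98% for correlations of 0.3 to 0.7. The SD, difference and group size are the article's; the profiles, the correlations and complete follow-up are assumptions.

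**What to change.** 1. **Primary objective:** reword to pain at 2 weeks, and move the course to 12 weeks to the secondary objectives.
2. **Data analyses:** state that time is a categorical visit factor and that the therapy difference at week 2 is the primary test.
3. **Baseline pain:** include it always, as a covariate or as a baseline response with the arms constrained equal, instead of leaving it to the 10% rule.
4. **Later visits:** report the differences at 4, 6 and 12 weeks from the same model as secondary results.

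The cost is a few sentences. The data, the visits, the software and the target of 135 patients stay as they are.

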### Secondary objectives

The study will assess the effectiveness of an IM gluteal corticosteroid injection versus an IM gluteal placebo injection in patients with hip OA with regard to function, mobility and patients' perceived improvement. Adverse reactions will be registered and an explorative subgroup analysis will be performed stratified for setting (general practitioner and outpatient clinics of department of orthopaedics).

## Methods

### Design

This is a double-blinded RCT. The Medical Ethics Committee of the Erasmus University Medical Center approved the trial (MEC2011-115). All patients will provide written informed consent.

### Patient selection

Patients with hip OA will be recruited in primary care (general practices in the Rotterdam area) and via hospital referrals (orthopaedic outpatient clinics in the Rotterdam area). Treating physicians are asked to select patients with hip OA and screen them on the inclusion/exclusion criteria (Table 1). If a patient has bilateral hip OA, the most painful hip will be selected as the study hip.

**Table 1 T1:** Patients' eligibility criteria

	Inclusion criteria:
1.	Hip OA* according to clinical ACR** criteria
2.	Age > 40 years
3.	Symptomatic disease for at least 6 months prior to enrolment
4.	Radiographic evidence of OA* (Kellgren-Lawrence score ≥ 2)
5.	Persistent pain despite receiving optimal doses of oral pain medication for at least 3 weeks. Pain severity (in rest or on walking) defined as ≥ 3 on an NRS^# ^(0-10 range, 0 = no pain)
	**Exclusion criteria:**
1.	Inability to understand Dutch questionnaires
2.	Systemic infection
3.	Local infection
4.	Systemic arthritis
5.	Diabetes mellitus
6.	Coagulopathy
7.	Gastric ulcer
8.	Current use of oral corticosteroids, DMARDs^$ ^or immunosuppressive medication
9.	Allergy to corticosteroids
10.	Anticoagulant therapy (coumarins)
11.	On the waiting list for total hip replacement surgery
12.	IA^## ^injection into the hip in the previous 6 months
13.	Radiologic signs of osteonecrosis
14.	Participation in other medical trial
15.	Pregnancy or lactating female

* *OA *Osteoarthritis; ***ACR *American College of Rheumatology; ^# ^*NRS *Numerical Rating Scale; $ *DMARD *disease-modifying antirheumatic drugs; ^## ^*IA *intra-articular

### Procedures

Eligible patients will receive written study information from their treating physician. If they show interest, the physician will fax their contact data to the research team. The researcher will contact the patient to answer additional questions. If the patient is interested/willing to participate, an appointment at the research centre will be made to sign an informed consent form and screen on inclusion/exclusion criteria, including assessment of radiologic hip OA. Pelvic anteroposterior (AP) X-rays taken within 6 months prior to enrolment are accepted; otherwise an AP pelvic X-ray will be taken. Two researchers will independently of each other assess grading of hip OA according to Kellgren-Lawrence (K&L) [11]. If the patient meets the radiologic criteria for participation (K&L score of ≥ 2), baseline measurement (questionnaire and physical examination) follows.

### Randomisation

An independent pharmacy assistant will allocate each patient based on computerized randomization lists to either receive placebo (saline) injection or triamcinolone acetate 40 mg injection IM. Randomization is stratified for setting (general practitioner and outpatient clinics of department of orthopaedics) and uses random blocks of 2 and 4.

### Blinding

To assure blinding with respect to the patient, researcher and treating physician, the trial medication will be packed and sealed by the pharmacy of the Erasmus MC, Rotterdam. An independent research assistant (who is not otherwise involved in the study) will prepare and administer, out of sight of the patient, the injection in the upper lateral quadrant of the gluteal musculature. The injection will be administered in the gluteal area ipsilateral of the study hip.

### Intervention

Patients who participate in the trial are randomized to either an IM triamcinolone acetate 40 mg injection once or an IM saline injection once.

Patients are allowed to continue their usual pain medication or physical therapy, but are requested not to start any new therapies regarding their hip OA during study follow-up.

### Outcomes

#### Questionnaires at baseline, 2, 4, 6 and 12 weeks

All outcomes are measured at baseline and at 2, 4, 6 and 12 weeks follow-up. The primary outcome is severity of hip pain reported by the patient at 2 weeks. This will be measured with two validated questionnaires: an 11-point numerical rating scale (NRS) in rest and on walking (0-10, where 0 equals no pain) [12], and the Western Ontario and McMaster University Osteoarthritis Index (WOMAC) pain subscale [13]. The WOMAC pain subscale will be converted to a 0-100 score, where 0 equals no symptoms. The WOMAC is recommended by the Osteoarthritis Research Society for use in clinical trials in patients with hip OA to measure pain and disability [13].

Secondary outcomes include the primary outcomes at 4, 6, and 12 weeks follow-up. Additional secondary outcomes are the disease-specific WOMAC function and stiffness subscales [13]. Both the function and stiffness subscale of the WOMAC will be converted to a 0-100 score. Data on pain and function will also be obtained with the Hip disability and Osteoarthritis Outcome Score (HOOS) [14], which was developed as an extended version of the WOMAC to evaluate the whole domain of patient-relevant outcome in young and active patients and is validated in the Dutch language [15].

For patients' perceived recovery a 7-point Likert scale will be used (score range 1 = 'worse than ever' to 7 = 'major improvement') [9,16]. Quality of life will be measured with the Euroqol (EQ-5D) [17]. Constant and intermittent pain will be obtained with the questionnaire Intermittent and Constant Osteoarthritis Pain (ICOAP) taking into account both pain intensity and impact on quality of life [18]. Patients' medical consumption will be registered and adverse reactions noted [9,16]. For this, a questionnaire will be used that covers the known local and systemic adverse reactions to corticosteroids. Data on daily pain and pain medication use will be obtained with a diary during the first 2-weeks follow-up.

Another secondary outcome is the difference in percentage of responders as defined by the OMERACT-OARSI (improvement in at least 2 of the 3 following domains: ≥20% improvement in WOMAC pain, ≥20% improvement in WOMAC function, or markedly improved on the patients' global assessment) [17].

At baseline various patient characteristics (gender, age, height, weight, race, education, marital status, occupational situation and co-morbidities) are recorded. Table 2 presents an overview of the parameters measured during follow-up.

**Table 2 T2:** Timing of measurements and outline of primary and secondary outcome measures

	Baseline	Daily diary for 2 weeks	2 weeks	4 weeks	6 weeks	12 weeks

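### Hip pain at week 2 is carried by several primary scores, but the sample size, alpha and power fit one primary test only, and no decision rule links them

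*Protocol article*

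**What the plan says.** The Outcomes section of the protocol article (Questionnaires at baseline, 2, 4, 6 and 12 weeks) defines one construct at one time point: "The primary outcome is severity of hip pain reported by the patient at 2 weeks". It then assigns more than one score to it: "This will be measured with two validated questionnaires: an 11-point numerical rating scale (NRS) in rest and on walking", followed by the WOMAC pain subscale, for which "The WOMAC pain subscale will be converted to a 0-100 score, where 0 equals no symptoms". Counted as variables, these are NRS at rest, NRS on walking and WOMAC pain. Table 2 has two rows under its primary heading, one for WOMAC pain and one for NRS pain.

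The plural returns elsewhere. The same section says "Secondary outcomes include the primary outcomes at 4, 6, and 12 weeks follow-up", and Data analyses plans the subgroup work by "assessing interaction effects between type of intervention and setting on the primary outcomes".

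The Sample size section treats the scales one after the other. For rest and walking pain (difference 10, SD 20) it concludes that "64 patients per group will be needed to show a statistically significantly difference using 80% power and with a 5% alpha". For WOMAC it says: "Assuming an SD of 16 and an 8-point difference as clinically relevant (effect size 0.5), the same sample size is needed". Allowing 5% loss, it arrives at 135 patients.

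Data analyses specifies linear mixed models for the continuous outcomes. It does not combine the primary scores, rank them, divide alpha among them or say what pattern of results counts as success.

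**The concern.** A claim of 5% alpha and 80% power belongs to a decision rule. Here the figures are computed for one test, while the outcome section and Table 2 give primary status to two or three. Which figure fails depends on how the scores are read together. If one significant score is enough, the false-positive rate exceeds 5%. If every score must be significant, power falls short of 80%.

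The practical risk comes at the end of the trial. If some scores reach significance and others do not, the protocol does not say whether the injection has been shown to work, and the criterion could then be chosen with the results in view.

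**Working it through.** **Inputs from the Sample size section.** Rest/walking pain: difference 10, SD 20, so d = 10/20 = 0.5. WOMAC: difference 8, SD 16, so d = 8/16 = 0.5. Alpha 5%, power 80%, loss 5%. Sidedness is not stated.

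**Reproducing the plan's figure.** n per group = 2(z₀.₉₇₅ + z₀.₈₀)²/d² = 2(1.960 + 0.842)²/0.25 = 62.8, so 63 by the normal approximation. The t-test version gives 63.77, so 64. Total: 128/0.95 = 134.7, so 135. A one-sided 5% would give 50 per group and does not match. The stated 64 and 135 are therefore those of one two-sided test at the full 5%, and the same calculation serves each scale. Power at 64 per group is 80.1% (t-test) or 80.7% (normal).

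**Assumptions for several scores.** The protocol gives no correlation between the scores, so an equal pairwise correlation ρ is assumed and varied. Test statistics are taken as multivariate normal with critical value 1.96. Under the alternative, every score has mean 0.5 × √(64/2) = 2.83. Results come from 2 million simulated draws per setting.

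**Check at ρ = 0.** Error for any of three = 1 − 0.95³ = 14.3%; for any of two = 1 − 0.95² = 9.75%. Power for all three = 0.807³ = 52.6%, against 52.7% simulated.

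| ρ | Three scores: error if any suffices | Three scores: power if all needed | Two scores: error if either suffices | Two scores: power if both needed |
|---|---|---|---|---|
| 0 | 14.3% | 52.7% | 9.8% | 65.3% |
| 0.5 | 12.6% | 62.3% | 9.1% | 69.7% |
| 0.7 | 10.9% | 66.9% | 8.3% | 72.3% |
| 0.8 | 9.8% | 69.7% | 7.8% | 73.8% |
| 0.9 | 8.4% | 73.0% | 7.1% | 75.9% |

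**Chance of a mixed result** (some but not all of three scores significant, d = 0.5 true for all) = chance of at least one minus chance of all. At ρ = 0.5: 95.3% − 62.3% = 33%. At ρ = 0.7: 92.4% − 66.9% = 26% (25.5%). At ρ = 0.8: 90.4% − 69.7% = 21%.

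**Can a rule hold both figures at 64 per group?**
- One named primary, or a fixed order: 5% error overall and 80.1% power for the first test.
- Bonferroni (0.05/3 = 0.0167 each) with any one score sufficing: error 4.4% to 3.5% and power 88% to 80% for ρ from 0.5 to 0.8. Power falls to 76% at ρ = 0.9, and power for any particular score is only 65.6%.
- At least two of three at 5% each: error 2.1% to 3.8% and power 85% to 82% for ρ from 0.5 to 0.8, but this error is controlled only when no score has an effect.

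By contrast, 80% power for each score under Bonferroni would need 86 per group (t-test). Requiring all three with 80% joint power would need 88 to 79 per group for ρ from 0.5 to 0.8.

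**The case against.** The strongest reply is that this is a condensed article and a separate analysis plan may set the testing order. Testing rules are commonly placed there, and their absence alone is no fault. That is fair. What remains is what the article itself fixes: several scores with primary status beside a sample size that fits only one. An analysis plan could supply the rule, but the choice of primary variable and the calculation that rests on it stand in this text and do not match.

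Three stronger conclusions are tempting, and the document does not support them.

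- A reader might infer that 5% and 80% cannot both be met with 135 patients. They can: a single named primary, a fixed order, or Bonferroni with any-one success meets both over the correlation range used here.
- A reader might take testing each score at 5% to be a stated rule. It is not. Data analyses gives no significance level; the undivided 5% is inferred from the sample size calculation.
- A reader might expect mixed results to be the likely outcome. At the design effect the chance is 21% to 33%, so agreement across scores is more likely.

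Two further limits stand. The count of primaries is open to reading: two instruments and two table rows, or three scores, which is why both are shown. And the figures describe a simple two-group comparison with an assumed correlation, not the planned mixed model with covariate adjustment, so they are illustrative.

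**Conclusion.** The point holds in this form: the protocol gives primary status to two or three week-2 pain scores, sizes each as a lone test, and leaves the link between them undefined. For correlations of 0.5 to 0.8, three scores give a familywise error of about 12.6% to 9.8% if any one suffices, or power of about 62% to 70% if all are required. Two scores give about 9.1% to 7.8%, or 70% to 74%. The power figures assume d = 0.5 on every score and 64 evaluable patients per group; all the figures assume equal correlations. The direction does not depend on the exact correlation: even at 0.9, three scores give 8.4% error or 73.0% power. The fault is the missing rule, not the size of the trial.

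**What to change.** Before unblinding, name one week-2 score as the single primary, tested at two-sided 5%; WOMAC pain and NRS on walking are examples. List the remaining scores in a fixed order, each tested at 5% only if the one before it is significant. Then make four places agree: the outcome paragraph, the primary rows of Table 2, the Sample size section (which score the 64 per group refers to, and that the test is two-sided) and the references to primary outcomes in the plural, including the one in Data analyses. If a separate analysis plan already contains such a rule, bring the protocol into line with it.

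The cost is a paragraph of wording. The sample stays at 64 per group and 135 in total, with no added measurements, and the first test keeps 5% alpha and about 80% power. The price is that the later scores can be claimed only in sequence: if the first fails, the others are descriptive.
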